#### Advertising for participants

Radio, newspaper, faith magazine, social media or television advertisements may also be used to publicise the study and encourage potential participants to get in touch with the researchers. Additionally, posters or flyers may be placed within the geographical area of recruiting sites in places such as supermarkets, libraries and community centres.

Individuals identified via any of the four approaches described above who wish to take part in the study will be asked to return their completed consent form and screening questionnaire by post to the YTU. Researchers will assess the screening form for participant eligibility according to the study eligibility criteria. Participants deemed to be ineligible will be informed in writing. If the respondent is assessed as being ineligible because they have not had a fall within the past 12 months or do not report a fear of falling, but otherwise fulfil the eligibility criteria, they will be given the option to be rescreened in 4–6 months’ time.

All eligible, consenting participants will be asked to complete a baseline questionnaire and monthly falls calendars by post. Participants who return a valid baseline questionnaire and at least one falls calendar will be randomised into the trial. Participants can withdraw from the study at any point. The reason for withdrawal will not have to be declared; however, if provided, this will be recorded. Participants who do not wish to take part in the main study are not required to return any forms to the YTU.

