### Inclusion criteria

Participants will be eligible for the OTIS trial if they:Are aged 65 years or over.Are willing to receive a home visit from an OT.Are community dwelling.Have at least one of the following risk factors for a fall in the next 12 months: either one fall in the past 12 months or report a fear of falling on their screening questionnaire.

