### Exclusion criteria

Participants will be ineligible for the OTIS trial if they:Are unable to walk 10 feet today (3.05 m) even with the use of a walking aid.Are unable to give informed consent, for example, due to Alzheimer’s disease or dementia.Live in a residential or nursing home.Are unable to read or speak English and have no friend or relative to translate/interpret for them.Have had an OT assessment for falls prevention in the previous 12 months.Are on a waiting list for an occupational therapy assessment.Have not returned at least one completed falls calendar in the 3 months prior to randomisation.

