### Randomisation

Participants will be enrolled into the study if they fulfil the eligibility criteria and provide written consent to take part in the study; they will then be randomised to either the intervention or control arm when they have returned a valid baseline questionnaire and at least one falls calendar within 3 months prior to the point of randomisation. Randomisation will be carried out using the YTU secure web-based computer randomisation service based on an allocation sequence generated by an independent data systems manager, who is not involved in the recruitment of participants. Participants will be randomly allocated to either the control group or the intervention group in a 2:1 ratio in favour of the control group (to reduce costs). Up to 12 participants from a particular site will be randomised at a time in a single block according to when sites state they have capacity to undertake intervention appointments and for how many participants. The allocation ratio used may go up to 3:1 in a block if the OTs have reduced capacity to carry out the assessment. The YTU will write to the participant’s GP informing them of study participation and to participants who are allocated to the intervention group.

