## Outcome measures

### Primary outcome measure for the OTIS trial

The primary outcome is the number of falls per participant over the 12 months from randomisation. A fall is defined as ‘an unexpected event in which the participant comes to rest on the ground, floor or lower level’.^22^ Data will be collected via participant self-reported monthly falls calendars, on which participants will be asked to mark the number of falls they have on each day or indicate that they have had no falls that month. An explanation of what the researchers consider to be a fall will be included in the participant information sheet and on the falls calendars. If a participant is uncertain as to whether an event is classed as a fall, then they will be encouraged to ring the research team at the YTU to discuss. Participants who do not return their falls calendar within 10 days of the due date will be either telephoned or sent a letter by the YTU to obtain missing data. Participants will be given a Freephone number to ring during office hours to report any falls as soon as possible after the event and when it is safe and convenient to do so. Participants who ring to report a fall will be asked for further details. Participants who indicate on their falls calendar that they have sustained a fall will be telephoned by the research team for further information. Information collected during the telephone call will include: cause/reason for fall and consequence of fall, for example, superficial wound (bruising, sprain, cut and abrasions), fractures (including type of fracture) and hospital admissions. Data collected from the 4-month, 8-month and 12-month follow-up questionnaires will include falls data and will be used for those participants who do not return their monthly falls calendars.

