### Statistical analysis of the OTIS primary outcome

The number of falls per person will be analysed using Poisson regression (or negative binomial regression, as appropriate) adjusting for gender, age, history of falling and the allocation ratio used to randomise the participant as fixed effects. The model will include an exposure variable for the number of months that the participant returned a monthly falls calendar. A sensitivity analysis will be conducted to account for potential clustering effects by the OT by assigning every randomised participant an OT irrespective of group allocation. For intervention participants, this will be the OT delivering their intervention, whereas for control participants, a counterfactual therapist, that is, one that they could have seen had they been randomised to the intervention group, will be randomly assigned to them. Therapist will then be included as a random effect in the primary analysis model. Additionally, a Complier Average Causal Effect analysis to assess the impact of compliance on treatment estimates will be undertaken for the primary analysis.

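### The primary model's covariate list does not name the falls calendars that every participant must return before randomisation, so some precision is probably given up

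*Protocol article*

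**What the plan says.** All references are to the Protocol article.

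- **Randomisation:** participants are allocated once they have "returned a valid baseline questionnaire and at least one falls calendar within 3 months prior to the point of randomisation". Exclusion criteria gives the same rule in the negative: "Have not returned at least one completed falls calendar in the 3 months prior to randomisation". It appears again under Advertising for participants: "Participants who return a valid baseline questionnaire and at least one falls calendar will be randomised into the trial".
- **Primary outcome measure for the OTIS trial:** on the calendars "participants will be asked to mark the number of falls they have on each day". These calendars are the main source of the primary outcome.
- **Statistical analysis of the OTIS primary outcome:** a Poisson or negative binomial model, "adjusting for gender, age, history of falling and the allocation ratio used to randomise the participant as fixed effects". The time term is also fixed: "The model will include an exposure variable for the number of months that the participant returned a monthly falls calendar".
- **Inclusion criteria:** the fall-risk condition is "either one fall in the past 12 months or report a fear of falling on their screening questionnaire".
- **Secondary analysis:** the logistic models and the repeated-event Cox model take the primary model's covariates. Continuous fear of falling is adjusted for its own baseline score and, as a separate term, for history of falling.
- **Missing data:** other pre-randomisation variables enter the primary model only in a sensitivity analysis, and only if they predict non-response.

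**The concern.** The run-in gives each randomised participant a count of falls recorded in the same way as the primary outcome. It is complete for at least one month by design. The baseline value of the outcome is often among the most useful covariates, and the plan uses one for fear of falling. For the primary outcome it names none, only history of falling with no source, window or coding.

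Much of the variance in an overdispersed count comes from differences between people in their underlying fall rate. A yes/no history cannot separate someone who fell once from someone who falls often. A recent prospective count can do so in part. At stake is the width of the confidence interval for the primary rate ratio, and some power, at no cost in participants or data collection. The validity of the comparison is not at stake.

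**Working it through.** **1. The plan's own figure.** Inputs from Sample size: 60% v 50% with at least one fall, 2:1, two-sided 5%, 90% power, 10% attrition.

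Pooled proportion = (0.5 + 2 × 0.6)/3 = 0.5667.

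Intervention n = [1.96 √(0.5667 × 0.4333 × 1.5) + 1.2816 √(0.25 + 0.24/2)]² / 0.1² = (1.1895 + 0.7795)²/0.01 ≈ 388. Control n = 776, total 1164, and 1164/0.9 = 1294 against 1299 stated. Power at 866/433 less 10% is 90.1%. At 974/325 less 10% it is 84.8%, against 85% stated. The figures reproduce. They rest on an unadjusted binary comparison, so no covariate choice alters them.

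**2. What one calendar can hold.** At an assumed 1.2 to 1.5 falls a year, one month carries 0.10 to 0.125 falls on average, so about nine in ten participants would score zero. The covariate is sparse but not empty.

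**3. Simulation of the gain.** The documents give no mean count or dispersion, so these inputs are assumptions:

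- Dispersion k = 0.5, 1 or 2.
- Control mean μ solved from 1 − (1 + kμ)^(−1/k) = 0.6, giving 1.16, 1.50 and 2.62 falls a year.
- Lognormal between-person variation, with 60% or 100% of its log-scale variance persisting from year to year. The run-in rate lies midway (geometric mean) between the past-year and follow-up rates.
- Run-in of 1 month, 3 months, or a mix of 1 to 3.
- History either yes/no or a 12-month count without recall error. No selection on eligibility and no treatment effect.
- Negative binomial fits on 60,000 subjects, with the standard error (SE) of the log rate ratio rescaled to 1299 × 0.9 analysed at 2:1. Run-in falls entered as indicators for 1, 2 and 3 or more, with terms for run-in months where these varied.

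Variance ratio = (SE with run-in falls / SE without)². Example with k = 2, 3 months, full persistence, yes/no history: (0.0631/0.0728)² = 0.751. Each cell gives 60% then 100% persistence.

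| k | Run-in months | History yes/no | History as count |
|---|---|---|---|
| 0.5 | 1 | 0.992, 0.989 | 0.994, 0.994 |
| 0.5 | 1 to 3 | 0.986, 0.977 | 0.989, 0.987 |
| 0.5 | 3 | 0.977, 0.965 | 0.982, 0.979 |
| 1 | 1 | 0.971, 0.958 | 0.982, 0.984 |
| 1 | 1 to 3 | 0.958, 0.928 | 0.973, 0.975 |
| 1 | 3 | 0.935, 0.901 | 0.957, 0.962 |
| 2 | 1 | 0.920, 0.852 | 0.960, 0.977 |
| 2 | 1 to 3 | 0.873, 0.801 | 0.931, 0.962 |
| 2 | 3 | 0.844, 0.751 | 0.912, 0.943 |

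All ratios are below 1. The reduction is about 1-25% for yes/no history and 1-9% for a count. With one month only, it is about 1-15% and 1-4%.

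**4. Translation to power.** Power = Φ(|ln RR|/SE − 1.96), with an illustrative rate ratio of 0.8 (assumed) and 1 to 3 months mixed.

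- Yes/no history, k = 1: SE 0.0733 to 0.0718 (60% persistence) and 0.0714 to 0.0687 (100%), so power rises from about 86-88% to 87-90%.
- Yes/no history, k = 2: SE 0.0764 to 0.0714 and 0.0727 to 0.0651, so power rises from about 83-87% to 88-93%.
- Count history: a gain of under 1 point at k = 1 and up to about 2 points at k = 2.

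**5. Cross-check with a single term.** A separate gamma-Poisson simulation used 779 v 390 analysed, a true rate ratio of 0.8, selection on eligibility, 60 replicates and run-in falls entered as log(1 + falls). At dispersion 1.5 with 2 months of run-in, yes/no history gave (0.0713/0.0753)² = 0.897 and log-count history gave (0.0625/0.0634)² = 0.972. Both lie within the ranges above.

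**The case against.** The strongest reply is that the article does not say the calendars go unused. History of falling has no stated source, window or coding. The inclusion criteria make a 12-month screening report the natural reading, but nothing rules out a covariate built from the run-in. A reader might infer that the model relies on recall alone and discards the calendars. The text does not establish that. It supports only the statement that the calendars are not named.

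A second reply is that covariate coding belongs in a statistical analysis plan, which is not shown and may settle the matter. This holds for the exact functional form. It is weaker for the covariate list itself, which the article fixes and passes on to the secondary models.

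A third reply concerns size, and much of it stands. Only one calendar is guaranteed, a one-month count is sparse, and the model already carries some prior-fall information. Entry is through a past fall or fear of falling, so fall history still varies among participants and is not emptied of information by selection. At dispersion 0.5 the gain is about 1-4% in every setting tried.

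Finally, the choice between a log count and a rate is a matter of judgement. That is a reason to fix one in advance, not to omit the term.

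**Conclusion.** The point holds as a modest, nearly free improvement. A mandatory baseline measure of the primary outcome is not named in the primary model, while fear of falling is given its own baseline term. Precision improved in every scenario tried: about 1-25% lower variance if history is yes/no and 1-9% if it is a 12-month count, with smaller gains where only one calendar is available.

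These figures rest on assumed means, dispersions, persistence of individual fall rates, run-in lengths and history coding, none of which the documents give.

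Two stronger readings should be resisted. The first is that the trial is biased or underpowered as planned. The randomised comparison is valid without the term, and the stated sample size reproduces without any covariate gain. The second is that the trial forgoes about a third of its effective size. A variance ratio of 0.751 does equal 1/0.751 = 1.33 in effective numbers. But that needs yes/no history, dispersion 2, three full run-in months and fully persistent fall rates together, and the documents support no such combination.

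**What to change.** Before the analysis, and without sight of outcome data by arm:

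1. Define history of falling: its source (screening form, baseline questionnaire or calendars), its window, and whether it is yes/no or a count. Keep it in the model.
2. Add falls recorded on pre-randomisation calendars to the primary model, for example log(1 + falls) with the number of run-in calendar months, or an equivalent rate. Fix one form in advance.
3. Carry the same term into the logistic and Cox models that take the primary model's covariates. Odds and hazard ratios are conditional on the covariates, so adding a term also changes slightly what they estimate. This is a further reason to settle it beforehand.

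The cost is one prognostic term plus one for run-in length, which varies between participants. The data are already collected, and at least one month is present for everyone by eligibility. No change to recruitment, follow-up or sample size is needed.

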### OTIS trial secondary outcomes

All secondary outcomes will be self-reported by the participant and collected via questionnaires at baseline, 4, 8 and 12 months or by monthly falls calendars. They include: proportion of participants reporting at least one fall in the 12 months from randomisation; proportion of participants reporting multiple (two or more) falls in the 12 months from randomisation; time to first fall from date of randomisation; health-related quality of life as measured by the EQ-5D-5L^23^; fracture rate; fear of falling as measured by the question ‘During the past 4 weeks have you worried about having a fall?’; and health service utilisation.

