### Secondary analysis

The following outcomes will be analysed by logistic regression adjusted for the same covariates as the primary analysis model: the proportion of participants who fall at least once over the 12-month period from the date of randomisation; the proportion of multiple fallers (two or more falls in the 12 months from randomisation); the proportion of participants having at least one fracture over the 12-month follow-up; the proportion of patients obtaining multiple fractures (from different events, if this occurs a sufficient number of times); and the proportion of participants who report that they are worried about falling at 12-month postrandomisation.

Fear of falling will also be analysed in its continuous form using a covariance pattern model incorporating all postrandomisation time points in the analysis and adjusting for baseline score, gender, age, history of falling, allocation ratio, treatment group, time and a treatment group-by-time interaction. The correlation of observations within patients over time will be modelled.

The time to the first fall will be derived as the number of days from randomisation until the patient reports having a fall as detailed in the participant’s falls calendars. Time between any subsequent falls will also be calculated. Participants who have not had a fall will be treated as censored at their date of trial exit, or date of last available assessment or 365 days/trial cessation, as appropriate. The proportion of patients yet to experience a fall will be summarised by a Kaplan-Meier survival curve for each group. Time to fall will be analysed using the Andersen and Gill method for analysing time to event data when the event can be repeated. The analysis treats each time to event or censoring as a separate observation. The data will be analysed by Cox proportional hazards regression using robust SEs to account for dependent observations by participant and adjusting for the same covariates as in the primary analysis model.

Adherence to the WeHSA and results of the TUG will also be summarised descriptively.

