### Missing data

The amount of missing data will be reported by trial arm. A comparison of the baseline characteristics of participants who are included in the primary analysis will be undertaken to ensure that any attrition has not produced imbalance in the groups in important baseline covariates. A logistic regression model will be used to predict non-response (no falls data received postrandomisation) including all variables collected prior to randomisation. The primary analysis will then be repeated, including as covariates all variables found to be significantly predictive of non-response, to determine if these affect the parameter estimates and study conclusions.

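### The primary model omits baseline fear of falling, one of the two entry risk factors: a small, avoidable loss of precision, with no bias

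*Protocol article*

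**What the plan says.** - **Entry.** Under Inclusion criteria, participants must "Have at least one of the following risk factors for a fall in the next 12 months", and the two that qualify are "either one fall in the past 12 months or report a fear of falling on their screening questionnaire".
- **Primary model.** Statistical analysis of the OTIS primary outcome specifies a Poisson or negative binomial model with an exposure term, "adjusting for gender, age, history of falling and the allocation ratio used to randomise the participant as fixed effects". Fear of falling is not listed, and no reason is given.
- **Measurement.** OTIS trial secondary outcomes lists "fear of falling as measured by the question" about worry over the past 4 weeks, among outcomes "collected via questionnaires at baseline, 4, 8 and 12 months or by monthly falls calendars". A baseline value will therefore exist.
- **Secondary models.** Secondary analysis applies the primary model's covariates to the logistic models and to the repeated-event Cox model. One of the logistic outcomes is being worried about falling at 12 months. The continuous fear model has a list of its own: "adjusting for baseline score, gender, age, history of falling, allocation ratio, treatment group, time and a treatment group-by-time interaction".
- **Sensitivity analysis.** Missing data repeats the primary analysis "including as covariates all variables found to be significantly predictive of non-response". Fear enters there only if it predicts non-response, not because it predicts falls.

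**The concern.** If the plan's own premise is right and fear predicts falls over the follow-up year, a prognostic baseline variable that is already in the database has been left out of the primary model. Fall history does not fully replace it. Everyone without a past fall must have entered through fear, but prior fallers may or may not be fearful, and the model cannot tell those two groups apart. What is at stake is the width of the interval on the primary rate ratio.

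A second consequence is easier to see. Because the logistic models inherit the primary list, the 12-month worry outcome is analysed without its own baseline value, while the continuous analysis of the same item does adjust for it.

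**Working it through.** **1. The plan's own figure.** For 60% v 50%, 2:1 allocation, two-sided 5% and 90% power, without continuity correction:
- pooled proportion = (0.5 + 2 × 0.6)/3 = 0.567
- smaller arm = [1.96 × √(1.5 × 0.567 × 0.433) + 1.282 × √(0.25 + 0.24/2)]² / 0.10² ≈ 388
- total = 388 + 776 = 1164, and 1164/0.9 ≈ 1294, against 1299 stated.

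Power with 10% attrition comes to 90.1% at 2:1 and 84.8% at 3:1, matching the stated 90% and 85%. The calculation takes no credit for any covariate, so leaving fear out does not make it wrong.

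**2. Assumed inputs for the gain.** None of these is in the article:
- mean 1.5 falls per year and negative binomial dispersion 1, which gives 1 − 1/(1 + 1.5) = 60% fallers, the article's control figure
- entry mix of 45% fall and fear, 25% fall only, 30% fear only
- fall-history rate ratio 1.8
- fear rate ratio 1.3, 1.5 or 2.0, given fall history
- 1169 analysed (1299 × 0.9), about 779 and 390 by arm.

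**3. What fear can add once history is in the model.** Yes/no fear is constant among the 30% without a fall history. Among the 70% with one, 0.45/0.70 = 64.3% are fearful. The residual variance of fear given history is 0.70 × 0.643 × 0.357 = 0.161.

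**4. Hand approximation.** With a log link, the omitted term adds about β² × 0.161 × (1/390 + 1/779) = β² × 0.000618 to the variance of the log rate ratio, where β is the log of the fear rate ratio. The standard errors (SE) without fear are those simulated in step 5.

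| Fear rate ratio | β² | Added variance | SE² without fear | Share |
|---|---|---|---|---|
| 1.3 | 0.0688 | 0.0000426 | 0.0812² = 0.00659 | 0.6% |
| 1.5 | 0.1644 | 0.000102 | 0.0811² = 0.00658 | 1.5% |
| 2.0 | 0.4805 | 0.000297 | 0.0811² = 0.00658 | 4.5% |

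**5. Direct fit.** Negative binomial models with and without fear were fitted to simulated data from the same scenario (true treatment rate ratio 0.8, 3000 runs per case).
- Mean SE fell from 0.0812 to 0.0809, from 0.0811 to 0.0805 and from 0.0811 to 0.0794.
- The model-based variance reductions are 0.7%, 1.6% and about 4%. Intervals narrow by roughly 0.3%, 0.8% and 2.1%.
- The empirical variance of the estimates, which is noisier, fell by 0.3%, 2.1% and 6.4%.
- In participants: 0.007 × 1299 ≈ 9, 0.016 × 1299 ≈ 21 and 0.04 × 1299 ≈ 52.

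**6. Other inputs.** A separate simulation with half of the prior fallers fearful and other dispersions gave effective sample size gains of 0.6%, 1.5–2.2% and 4.2–6.0%. With a fear rate ratio of 1.0 the gain was nil.

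**7. Bias.** In both simulations the treatment log rate ratio was off by no more than about 0.01, and in the second the error was much the same with and without fear. In the first, coverage without fear was 95–96%.

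**The case against.** The case for leaving the list alone is strong. A short, prespecified list containing the factor closest to the outcome is a legitimate choice, and no rule makes every entry criterion a covariate. The gain is capped because yes/no fear tells the model nothing about participants without a past fall. Fear may also overlap with age, gender and the number of past falls, which the calculation ignores, and that tends to flatter its contribution. All of this stands.

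A reader might infer more than the article supports:
- **That the treatment effect is biased.** It is not. Fear is a baseline variable in a randomised comparison.
- **That chance imbalance in fear is a second harm.** With 75% fearful, its standard deviation between arms is √(0.75 × 0.25 × (1/866 + 1/433)) ≈ 0.025. At a fear rate ratio of 1.5 that shifts the log rate ratio by about 0.025 × 0.405 = 0.010, against an SE of about 0.08. Step 4 of the working shows that this is the same variance already counted, not an addition to it.
- **That the gain is about twice as large.** Taking the variance per participant as 1/mean plus a moment-matched dispersion gives reductions of 1.5%, 3.3% and 8.0% in this scenario. Fitting the models directly gives about half of that.
- **That the plan contradicts itself or that 1299 is wrong.** Neither follows.

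The objection does not reach the 12-month worry model, where the same item is adjusted for baseline in one analysis and not in the other.

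**Conclusion.** The point holds as a minor matter of efficiency. The primary model leaves out a variable that the plan itself calls a risk factor and already collects. Under the assumed inputs the cost is about 0.7%, 1.6% or 4% of the variance of the log rate ratio for fear rate ratios of 1.3, 1.5 or 2.0, and zero if fear has no effect beyond fall history. The size rests wholly on a fall rate, dispersion, entry mix and rate ratios that the article does not give. Only the direction follows from its own premise.

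These percentages are for the primary rate ratio. They do not carry over directly to the logistic and Cox models, where adjusting for a prognostic covariate also changes the conditional effect being estimated. The inconsistency in the 12-month worry analysis needs no assumed inputs and is the clearest reason to act.

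**What to change.** Before the data are analysed, add the baseline 4-week worry response to the fixed effects of the primary model, so that it carries into every secondary model using the same covariates. The graded response is preferable to the yes/no screening item because it can also vary among those who entered through fear alone. State a simple rule for missing baseline answers; there should be few, since a valid baseline questionnaire is required before randomisation. If the primary list is to stay as it is, at minimum add the baseline value to the 12-month worry model so that it matches the continuous analysis.

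The cost is one prespecified covariate and one sentence on missing values. No new data collection and no change to the sample size are needed.

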**Methods and analysis:**

A two-arm, modified cohort randomised controlled trial, conducted within England, with 1299 community-dwelling participants aged 65 years and above, who are at an increased risk of falls. Participants will be randomised 2:1 to receive either usual care or home assessment and modification. The primary outcome is rate of falls (falls/person/time) over 12 months assessed by monthly patient self-report falls calendars. Secondary self-reported outcome measures include: the proportion of single and multiple fallers, time to first fall over a 12-month period, quality of life (EuroQoL EQ-5D-5L) and health service utilisation at 4, 8 and 12 months. A nested qualitative study will examine the feasibility of providing the intervention and explore barriers, facilitators, workload implications and readiness to employ these interventions into routine practice. An economic evaluation will assess value for money in terms of cost per fall averted.

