### Blinding

Control participants will be blinded to when the intervention takes place; however, due to the nature of the intervention, participants in the intervention group will not be blind. It is also not possible to blind members of the research team who are actively involved in the administration of the study, the statistician or health economist. Data entry staff will be blind to group allocation.

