## Statistical analysis

There are no planned interim analyses; therefore, the statistical analysis will be undertaken at the end of the trial and will be conducted using STATA V.15 or later. All analyses will be conducted on an intention-to-treat (ITT) basis, including all randomised patients in the groups to which they were originally allocated. Participant baseline data will be summarised descriptively by group, for all those who have been randomised and for all those who are included in the primary outcome analysis by randomised arm. No formal statistical comparisons will be undertaken. Continuous measures will be reported as means and SD, while the categorical data will be reported as counts and percentages.

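### The primary model's exposure counts only months with a returned calendar, but questionnaire falls are also to be used, so falls and person-time do not match

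*Protocol article*

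**What the plan says.** All references are to the protocol article.

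- **Outcome.** *Primary outcome measure for the OTIS trial*: "The primary outcome is the number of falls per participant over the 12 months from randomisation".
- **Second source of falls.** The same section says of the 4-, 8- and 12-month questionnaires that the data "will include falls data and will be used for those participants who do not return their monthly falls calendars". Late calendar returners are also telephoned or written to for the missing data, and falls can be reported by Freephone.
- **Model.** *Statistical analysis of the OTIS primary outcome*: "The number of falls per person will be analysed using Poisson regression (or negative binomial regression, as appropriate").
- **Exposure.** The same section: "The model will include an exposure variable for the number of months that the participant returned a monthly falls calendar". Time covered by a questionnaire is not mentioned.
- **Analysis set.** *Statistical analysis* describes intention to treat, "including all randomised patients in the groups to which they were originally allocated".
- **Non-response.** *Missing data*: "A logistic regression model will be used to predict non-response (no falls data received postrandomisation"). On this definition, someone with questionnaire falls data only is a responder.

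**The concern.** A Poisson or negative binomial rate model is valid only if the falls counted and the time entered as exposure cover the same period. Here the falls may come from two sources, while the exposure recognises one. No section adds questionnaire time to the exposure, and none keeps questionnaire falls out of the primary count.

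This is the primary analysis. Calendar return is participant behaviour in an open trial. The *Blinding* section notes that "due to the nature of the intervention, participants in the intervention group will not be blind", and only the intervention arm receives an OT visit and a call four weeks later. Return could therefore differ by arm. If it did, the difference would pass into the estimated rate ratio, in either direction.

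**Working it through.** **The plan's own figures.** The plan gives no number for calendar return, fall rate or dispersion, so there is nothing to reproduce on this point. The sample size reproduces closely (60% v 50%, 2:1, 90% power, two-sided 5%: 776 + 388 = 1164; 1164/0.9 = 1294 against 1299 stated). It rests on a binary outcome and is unaffected.

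**Step 1. One participant, two readings of the questionnaire sentence.**

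- *Gap filling.* With *m* calendars and questionnaires covering the rest, 12 months of falls are divided by *m* months. The rate is inflated by up to 12/*m*: 12/8 = 1.5, 12/6 = 2, 12/4 = 3.
- *No calendars at all.* Exposure is 0, log(0) is undefined, and the participant drops out of the model although their falls are known.

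**Step 2. Rate ratio under no true effect (gap filling).** Let a share *s* of an arm be partial returners with *m* of 12 calendars and full questionnaire recovery. Then:

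- observed rate / true rate = 1 / [(1 − *s*) + *s·m*/12]
- null ratio = [(1 − *s*C) + *s*C·*m*/12] / [(1 − *s*I) + *s*I·*m*/12], with C for control and I for intervention

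This is the ratio of crude totals, which is also what a Poisson fit with treatment alone returns. All inputs are assumed.

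| Partial return, control v intervention | 8 calendars | 6 calendars | 4 calendars |
|---|---|---|---|
| 20% v 20% | 1.000 | 1.000 | 1.000 |
| 20% v 10% | 0.966 | 0.947 | 0.929 |
| 10% v 20% | 1.036 | 1.056 | 1.077 |
| 10% v 5% | 0.983 | 0.974 | 0.966 |

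Example: 20% v 10% with 6 calendars is 0.90/0.95 = 0.947. If the questionnaires recover only half of the uncovered falls, the same case gives 0.972.

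**Step 3. Negative binomial fit.** This model weights participants more equally than crude totals do, so the inflated individual rates count for more. With fully equal weights and 6 calendars, the mean inflation is 1 + *s*. The null ratio is then 1.10/1.20 = 0.917 for 20% v 10%, and 1.05/1.10 = 0.955 for 10% v 5%. The fitted value should lie between these and the crude 0.947 and 0.974.

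Simulation, true ratio 1.00, 6 of 12 calendars, full recovery, 300 replicates per row:

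| Assumptions | Partial return, control v intervention | Rate ratio | Type I error |
|---|---|---|---|
| 866 v 433, 1.5 falls/year, dispersion 1 | 20% v 10% | 0.93 | 18% |
| same | 10% v 20% | 1.07 | 19.7% |
| same | 20% v 20% | 1.00 | 7% |
| 779 v 390 (less 10% attrition), 1.7 falls/year, dispersion 1.2 | 20% v 10% | 0.92 | 16% |
| same | 10% v 20% | 1.07 | 13% |
| same | 20% v 20% | 1.00 | 6% |

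At 300 replicates, a type I error near 18% carries a 95% Monte Carlo margin of about 1.96 × √(0.18 × 0.82/300) = 4.3 points, so the 19.7% is not distinct from the others. A repeat with 1,000 replicates gave 17 to 18% for all four 10-point rows, with ratios of 0.93 and 1.07 to 1.08. It gave about 0.96 and 1.04 for 5-point imbalances (10% v 5% and 5% v 10%).

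**Step 4. Matched falls and time.** For 20% v 10% under the first set of assumptions, calendar falls over calendar months, and all falls over all months covered, both give about 1.00 with 3% type I error. With a true ratio of 0.80, the mismatched model gives about 0.74 and either matched version gives 0.80.

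**The case against.** The strongest reply is that a consistent reading exists. The abstract defines the outcome from calendars: "The primary outcome is rate of falls (falls/person/time) over 12 months assessed by monthly patient self-report falls calendars". That fits calendar-month exposure, and questionnaire falls could then serve only the binary faller outcomes, which need no exposure. How sources combine is also commonly left to the SAP, which is not shown. This does not dispose of the point. The questionnaire sentence sits inside the primary outcome definition, and the article is not silent on exposure: it states a rule that does not fit its own data sources.

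Several other objections stand in part:

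- The questionnaire sentence may mean only participants with no calendars. Then rates are not inflated and the fault is lost data. That group may be small, because a calendar is required before randomisation and late returners are chased. *Statistical analysis* also already foresees a primary analysis set distinct from all randomised. Even so, people counted as responders under *Missing data* could not enter the model.
- Six missing months do not tile neatly if each questionnaire covers four months (the recall period is not stated). The 4- and 8-calendar columns do tile and show the same behaviour.
- Chasing is described without distinction by arm, and control participants do not know when they were randomised. Equal return is therefore possible, and it leaves the ratio unbiased.

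**Conclusion.** The two rules do not fit together as written, on either reading. With gap filling, arm-specific rates are inflated, and the rate ratio is biased only if calendar return (or questionnaire recovery) differs by arm. With questionnaire-only participants, exposure is zero and known data are lost.

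On the assumed inputs above, a 10-point imbalance gives a null ratio of about 0.92 to 1.07 and a type I error of about 13 to 18%. A 5-point imbalance gives about 0.96 to 1.04, and equal return gives no bias in the ratio. The document supplies none of these inputs, so neither the size nor the direction in this trial can be determined.

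Three stronger conclusions are not supported:

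- A reader might infer that the trial's rate ratio is, or will be, biased. The document gives no evidence that return differs by arm.
- A reader might set these ratios beside the 0.88 in the Introduction and conclude that the artefact matches the effect sought. That figure is a review's relative risk of falling, and this trial is powered on 60% v 50% with at least one fall. Neither is a rate ratio.
- A reader might add that calendars straddle the 12-month window. No calendar start dates are given, and falls are marked by day, so they can be assigned by date.

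**What to change.** Reconcile the two sections in one of two ways, before any analysis by arm.

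1. **Match the exposure to the sources.** In *Statistical analysis of the OTIS primary outcome*, replace the exposure sentence with: *Exposure is the time from randomisation, up to 12 months, covered by whichever source supplied the falls that are counted; time covered by no source contributes neither falls nor exposure.* State the period that each questionnaire covers, and which source is used where a questionnaire overlaps returned calendars, so that no fall is counted twice. Add a sensitivity analysis of calendar falls over calendar months only.
2. **Match the falls to the exposure.** Keep the exposure sentence, restrict the primary count to calendar falls over calendar months, and amend the questionnaire sentence in the primary outcome section. Use questionnaire falls, with their time, in a sensitivity analysis. Say that participants with no calendars are then outside the primary model.

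Either is acceptable. The first keeps more participants, but it pools recalled falls with daily records and may undercount; its calendar-only analysis addresses that. The cost is a sentence or two of protocol and SAP wording and one derived variable, with no new data.
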